#### Safety variable analysis

2.8.3

Safety evaluations will assess the frequency of adverse events suspected to be treatment-related, as well as serious adverse events. Adverse events will be collected through patient self-reports and investigator observations. All observed adverse events will be described in detail, with frequencies of events related and unrelated to the trial intervention presented using descriptive statistics. Group comparisons of adverse events related to medication administration will be conducted using the chi-square test or Fisher’s exact test. Additionally, safety evaluation variables, including AST, ALT, BUN, Cr, and vital signs (blood pressure, pulse rate, and temperature), will be analyzed for pre–post treatment differences using the paired t-test or the Wilcoxon signed-rank test.

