#### Study design and allocation

2.1.1

This study is a randomized, assessor-blinded, parallel-group, open-label, multicenter clinical trial. It will be conducted at two Korean medical hospitals: Kyung Hee University Hospital at Gangdong and Dongguk University Ilsan Oriental Medical Hospital. Participants who voluntarily sign the informed consent form will undergo screening examinations during their initial visit (screening visit), including interviews, vital sign measurements, questionnaire surveys, assessments with Korean medicine diagnostic devices, and laboratory tests. Eligible participants will then be enrolled. Within 2 weeks of the screening visit, participants will be randomly assigned to either the ACCORD group, which will receive YJT, PWS, or SST based on a machine learning–driven herbal response prediction algorithm, or the DISCORD group, which will be randomly assigned one of the two herbal medicines not selected by the prediction algorithm from the three options. This ACCORD vs. DISCORD design is specifically employed to validate the algorithm’s discriminative ability—that is, whether the algorithm can accurately distinguish the optimal treatment from suboptimal alternatives for an individual patient. This validation of predictive accuracy is a necessary step before evaluating clinical utility against standard care.

The machine learning algorithm employed in this trial was developed in a prior preliminary clinical study (*N* = 265) (19) (the resulting paper detailing the development methodology is currently under review; Supplementary material 1). The algorithm utilizes the XGBoost (Extreme Gradient Boosting) regressor framework. The objective of the model is a regression task: to predict the magnitude of symptom improvement (effect size) for each of the three herbal formulations (YJT, PWS, and SST). The prediction system recommends the formulation expected to yield the greatest therapeutic benefit for the individual.

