#### Randomization and blinding

2.1.2

Participants will be divided into the ACCORD group, assigned herbal medication by the machine learning-based prediction algorithm, and the DISCORD group, which will not use the prediction algorithm. For example, if the prediction algorithm assigns YJT, the group receiving YJT will constitute the ACCORD group, whereas those receiving PWS or SST will constitute the DISCORD groups. Randomization will be stratified by each herbal medicine using block randomization to minimize bias before the clinical trial begins. For each stratification factor, the group allocation ratio will be 1:1 (ACCORD: DISCORD), with block sizes of 4 and 8. The DISCORD group will then be divided into two subgroups, excluding the optimal herbal medicine per the prediction algorithm, and randomly assigned, resulting in a 2:1:1 allocation (ACCORD: DISCORD_1: DISCORD_2). To prevent bias toward a specific herbal medicine, the maximum number of participants assigned to any single herbal medicine will be capped at 48. Any additional participants for that medicine will be excluded during screening.

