### Sample size calculation

2.7

Participants will be randomly assigned to either the ACCORD group, which will receive YJT, PWS, or SST based on the machine learning–driven prediction, or the DISCORD group, which will not use the machine learning-based prediction for herbal assignments. Based on preliminary clinical trial results (19), the mean change in the GIS score after 8 weeks in both the ACCORD and DISCORD groups is assumed to be 2.72, with a standard deviation of 4.57. To meet this requirement, each group will require 45 participants. Considering a 10% dropout rate, the total required sample size is 100 participants. This sample size was determined for the prespecified primary comparison (ACCORD vs. pooled DISCORD) and was not inflated to power subgroup or stratified analyses, which will be considered exploratory.

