### Statistical analysis

2.8

All statistical analyses will be conducted using two-sided tests with a significance level of 5%. For continuous data, means and 95% confidence intervals will be presented, whereas categorical data will be presented as frequencies and percentages. All analyses will be performed using SAS® Version 9.4 (SAS Institute Inc., Cary, NC, United States).

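### The only between-group adverse-event test stated appears to be ACCORD versus DISCORD; both arms can contain all three formulas, so a formula-specific harm is diluted, cancelled or reversed in it

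*Protocol article*

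**What the plan says.** Section 2.8.3 (Safety variable analysis) contains three elements:

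- **Description.** All adverse events are described, with frequencies of related and unrelated events. No breakdown by formula is stated.
- **Between-group test.** "Group comparisons of adverse events related to medication administration will be conducted using the chi-square test" or Fisher's exact test. The section does not say which groups are compared.
- **Within-patient tests.** AST, ALT, BUN, creatinine and vital signs "will be analyzed for pre–post treatment differences using the paired t-test or the Wilcoxon signed-rank test". No grouping by formula is stated here either.

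The arms are defined in sections 2.1.1 and 2.1.2. One is "the ACCORD group, which will receive YJT, PWS, or SST based on a machine learning–driven herbal response prediction algorithm". The other, DISCORD, is randomised to one of the two formulas that the algorithm did not select. Randomisation is stratified by formula, "resulting in a 2:1:1 allocation (ACCORD: DISCORD_1: DISCORD_2").

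Section 2.8.2 plans exploratory analyses by assigned formula and by DISCORD subgroup. They sit in the efficacy section and run within the mixed model; nothing extends them to adverse events. Section 2.8 sets the test level: "All statistical analyses will be conducted using two-sided tests with a significance level of 5"%.

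**The concern.** ACCORD and DISCORD differ in how a formula was chosen. A pharmacological adverse reaction depends on which formula was taken. Table 2 shows three products of different composition, and section 2.9.2 discusses expected reactions separately for YJT, PWS and SST. As long as each formula is recommended to some patients, both arms contain all three. An excess of events on one formula then appears in both arms and partly or wholly subtracts out of their difference.

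A report that follows section 2.8.3 to the letter could therefore state that adverse events did not differ between groups while one formula had several times the event rate of the others. Nothing else stated in the section would show this: the descriptive frequencies and the pre–post tests are not split by formula.

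**Working it through.** **Inputs from the article.** 50 patients per arm (abstract); two-sided 5% level (section 2.8); 2:1:1 allocation within each recommendation stratum (section 2.1.2); a cap of 48 on the number assigned to any one formula (section 2.1.2).

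**Inputs not in the article, assumed here.** Medication-related event rates of 5% on two formulas and 20% or 30% on the third; recommendation share a of the third formula, varied from 0.10 to 0.92.

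**The plan's own figure.** Section 2.8.3 gives no power or detectable difference for safety. The arm size comes from the efficacy calculation in section 2.7: 2 × (1.960 + 0.842)² × (4.57/2.72)² = 44.3, so 45 per arm, and 45/0.9 = 50. This matches the stated size, but only at 80% power and with 2.72 read as the between-group difference, neither of which the section states. It bears on the present point only by fixing 50 per arm.

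**Step 1: mix within each arm.** A formula recommended to share a makes up a of ACCORD. In DISCORD it goes to half of those for whom it was not recommended, that is (1 − a)/2.

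**Step 2: what reaches the arm contrast.** If that formula has excess risk d over the other two, the ACCORD − DISCORD difference is

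d × [a − (1 − a)/2] = d × (3a − 1)/2.

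| Share a | Part of d that survives |
|---|---|
| 0.10 | −35% |
| 0.20 | −20% |
| 1/3 | 0% |
| 0.40 | +10% |
| 0.48 | +22% |
| 0.60 | +40% |
| 0.80 | +70% |
| 0.92 | +88% |

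**Step 3: which shares are possible.** The number taking the formula is 50a + 50(1 − a)/2 = 25(1 + a). If the cap of 48 counts patients for whom the formula is recommended, a is at most 0.48. If it counts patients who receive it, 25(1 + a) ≤ 48 allows a up to 0.92. The article does not settle which.

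**Step 4: arm rates and rejection probability** (exact enumeration, Fisher's test, 50 vs 50).

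- 20% vs 5%, a = 1/3: (0.20 + 0.05 + 0.05)/3 = 10.0% in both arms; rejection 0.018.
- 20% vs 5%, a = 0.48: 0.48 × 0.20 + 0.52 × 0.05 = 12.2% in ACCORD and 0.26 × 0.20 + 0.74 × 0.05 = 8.9% in DISCORD; rejection 0.036.
- 30% vs 5%, a = 1/3: 13.3% in both arms; rejection 0.022.
- 30% vs 5%, a = 0.48: 17.0% vs 11.5%; rejection 0.069.

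**Step 5: the same 100 patients by formula taken** (that formula against the other two pooled, Fisher's test).

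- a = 1/3, so 25 × 4/3 ≈ 33 vs 67: power 0.57 for 20% vs 5%, and 0.90 for 30% vs 5%.
- a = 0.48, so 25 × 1.48 = 37 vs 63: power 0.57 and 0.90.

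An exact test of the three formulas as separate groups (33/33/34) has power of about 0.50 for 20% vs 5%.

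**Step 6: the favourable extreme.** At a = 0.92 and 20% vs 5%, the arm rates are 18.8% and 5.6%. By normal approximation the power is 0.52 between arms, against 0.63 by formula taken. The loss is then small.

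**The case against.** **The groups are inferred.** Section 2.8.3 names no groups, and section 2.1.2 also speaks of two DISCORD subgroups. By-formula safety tables could stand in an analysis plan that is not shown. This stands as a limit on the wording: one may say that the only stated between-group adverse-event test is most naturally ACCORD versus DISCORD, but not that comparison by formula is excluded. It does not remove the point. Section 2.8.2 uses between-group for ACCORD versus DISCORD, and the article states a by-formula analysis for efficacy but none for safety.

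**Other safety looks exist.** A reader might infer that this is the trial's only safety test. It is not: pre–post tests and frequencies of all adverse events are planned, and section 2.10 has the study team monitor safety and review serious events immediately on report. These do not close the gap in the stated analysis, because none is described by formula. A reader might also infer that relatedness is judged with knowledge of the allocation; the article does not say who judges it.

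**The arm contrast is legitimate.** A reader might conclude that it answers no safety question and should be replaced. That goes too far. The selection rule is what is randomised 1:1, and whether it changes the burden of adverse events is a fair question. Formula taken, by contrast, is tied to the recommendation, which is built from baseline symptoms and laboratory results (section 2.1.1). A crude by-formula comparison is therefore confounded. This stands and shapes the fix.

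**The example is assumed.** Nothing in section 2.9.2 suggests a gap of 20% versus 5% between formulas. The 57% also supposes that the suspect formula is compared with the other two pooled; with three separate groups it is about 50%. Both remarks are correct. The dilution factor (3a − 1)/2 does not depend on the assumed rates.

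**Conclusion.** The point holds in a limited form. On its natural reading, the one between-group adverse-event test stated carries only (3a − 1)/2 of a formula-specific excess risk. Complete cancellation needs a recommendation share of exactly one third. Elsewhere the signal is diluted, and below one third it points against DISCORD. If the cap applies to recommendations, at most 22% survives for a formula recommended to more than a third of patients; if it applies to receipt, up to 88% can survive.

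Under the assumed 20% vs 5%, the arm test rejects about 2–4% of the time for shares of one third to 0.48, against about 57% by formula taken. The result rests on the arm reading of the groups, on assumed event rates and shares, and on 50 analysed patients per arm. It does not show that any formula is harmful, or that the arm comparison is wrong in itself. It shows that the stated comparison cannot be relied on to reveal a difference between products.

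**What to change.** In section 2.8.3:

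1. Name the groups in the adverse-event comparison and keep ACCORD versus DISCORD.
2. Add a tabulation, by formula actually taken (YJT, PWS, SST), of all adverse events, related and unrelated, and of the laboratory changes.
3. Add a descriptive by-formula comparison of adverse events stratified by recommended formula. Within each stratum patients are randomised 2:1:1 among the three formulas, so the comparison there rests on randomisation.

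The cost is some wording and a few tables. The by-formula comparison is exploratory: power is limited even for a fourfold rate, stratifying makes the cells smaller, and it should be labelled accordingly. No new data are needed if week-8 bloods are taken. Sections 2.1.1 and 2.5.3 plan them, but Table 1 marks the blood test only at screening, so these places should be reconciled.

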#### Exclusion criteria

2.2.2

Diagnosis of organic diseases such as peptic ulcers, esophageal cancer, MALT lymphoma, gastric cancer, colorectal cancer, or biliopancreatic diseases (asymptomatic gallstones are exempted) within 1 year prior to screening.Symptoms of gastroesophageal reflux disease or irritable bowel syndrome that are more severe than dyspepsia symptoms.Presence of alarm symptoms, including severe weight loss, hematochezia, dysphagia, odynophagia, or persistent vomiting.Significant neurological or psychiatric history or current conditions, including major depressive disorder, anxiety disorder, schizophrenia, anorexia nervosa, or epilepsy.Serious organic diseases (e.g., heart failure, angina, myocardial infarction, arrhythmia, valvular disease, malignant tumors, or stroke).History of gastrointestinal surgery (appendectomy permitted if performed more than 6 months prior to trial participation).Use of medications affecting the gastrointestinal tract, such as proton pump inhibitors, histamine receptor antagonists, antacids, gastrointestinal motility agents, fundus relaxants, mucosal protective agents, anticholinergics, adsorbents, antiflatulents, antiemetics, emetics, gastrin receptor antagonists, prostaglandin analogs, or *Helicobacter pylori* eradication therapy within 2 weeks prior to screening.Receipt of Korean traditional treatments such as acupuncture, herbal medicine, or moxibustion for dyspepsia within 2 weeks prior to screening or plans to receive such treatments during the study period.Use of antibiotics within 3 months prior to screening.Use of probiotic supplements within 1 month prior to screening (participation allowed if probiotics have been taken continuously for more than 1 month prior to screening without planned dosage changes during the trial).Severe liver or kidney dysfunction (as defined by AST or ALT levels more than three times the upper limit of normal, or serum creatinine levels more than twice the upper limit of normal at screening).History of significant alcohol or substance abuse.Pregnant or breastfeeding women, or women of childbearing potential unwilling to use effective contraception during the trial period.Conditions such as galactose intolerance, Lapp lactase deficiency, or glucose–galactose malabsorption.Known hypersensitivity to investigational medicinal products.Use of other investigational medicinal products within 3 months prior to the study.Chronic diseases not well controlled despite appropriate treatment (posing life-threatening risks, requiring hospitalization, causing severe physical disability, or substantially affecting daily life due to conditions such as hypertension or diabetes).Determined unsuitable for trial participation by the investigator or trial director for any other reason.

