#### Safety evaluation variables

2.5.3

Liver function tests (AST, ALT) and renal function tests [blood urea nitrogen (BUN), creatinine (Cr)] will be conducted at screening and at week 8, requiring participants to fast for at least 8 h beforehand. Vital signs, including blood pressure (systolic and diastolic), pulse rate, and body temperature, will be measured. Blood pressure and pulse rate will be recorded in a seated position using an electronic sphygmomanometer after a minimum of 3 min of rest, except during telephone visits. Body temperature will be measured with an electronic thermometer after blood pressure measurement. Adverse events will be collected through participant self-reporting or investigator observation during the clinical trial.

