#### Adverse events and serious adverse events

2.9.1

Adverse events (AEs) are defined as undesirable and unintended signs, symptoms, or diseases that occur in participants during a clinical trial, regardless of whether they are causally related to the investigational treatment. AEs are identified through vital sign measurements, participant self-reports, investigator observations, and AE monitoring. Any clinically significant symptoms or changes, as determined by the investigator, are considered AEs and must be documented in the case report form, including details of occurrence, evaluation, and management. Medical events that occur before the administration of the investigational product are documented as medical history, while AEs occurring after trial completion are reported only if they are classified as serious and deemed related to the investigational product.

Serious adverse events (SAEs) are defined as any AE occurring at any dose of the investigational product that results in one or more of the following: (1) death or life-threatening events, (2) hospitalization or prolonged hospitalization, (3) permanent or significant disability/incapacity, (4) congenital anomaly or birth defect, or (5) other medically important conditions, such as drug dependence or abuse, blood disorders, or other significant medical events.

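### The stated pre–post tests of AST, ALT, BUN and creatinine are nearly blind to one to three isolated severe rises; counts above a limit, by formula received, would show them

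*Protocol article*

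**What the plan says.** Safety variable analysis (2.8.3) starts with adverse events: "All observed adverse events will be described in detail, with frequencies of events related and unrelated to the trial intervention presented using descriptive statistics". It adds a between-group test for medication-related events. It then turns to the laboratory values and vital signs, which "will be analyzed for pre–post treatment differences using the paired t-test or the Wilcoxon signed-rank test". It states no other analysis for AST, ALT, BUN or creatinine, and no rule for choosing between the two tests.

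Safety evaluation variables (2.5.3) says that the liver and renal tests "will be conducted at screening and at week 8, requiring participants to fast for at least 8 h beforehand".

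Numerical limits appear in Exclusion criteria (2.2.2) only: "Severe liver or kidney dysfunction (as defined by AST or ALT levels more than three times the upper limit of normal", and "serum creatinine levels more than twice the upper limit of normal at screening".

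Adverse events and serious adverse events (2.9.1) gives a second route by which an abnormal result could be reported: "Any clinically significant symptoms or changes, as determined by the investigator, are considered AEs and must be documented in the case report form". The sources listed there are these: "AEs are identified through vital sign measurements, participant self-reports, investigator observations, and AE monitoring".

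**The concern.** Laboratory safety tests can answer two questions: whether values drift across the group, and whether any individual has a marked rise. The stated tests address the first. For the second, the paired t-test has a structural weakness: one extreme value raises the mean a little but inflates the standard deviation as well. The signed-rank test reduces the same value to a single high rank.

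If harm falls on a few participants, the laboratory section of the report could therefore show no significant change while someone has an ALT several times the upper limit. Whether the reader hears of that person would then depend on an investigator's judgment of clinical significance in an open-label trial. Monitoring (2.10) also says that there will be no independent data monitoring committee.

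**Working it through.** **Inputs from the article.** Two-sided 5% level (2.8); 45 evaluable participants per group, 100 in total with 10% dropout (2.7); limits of 3 × ULN for AST/ALT and 2 × ULN for creatinine (2.2.2). The article gives no figure for the laboratory analysis itself and does not say whether the paired test is run per group or pooled.

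**The plan's own figure.** Read 2.72 as the between-group difference, take SD 4.57, and assume 80% power, which the article does not state. Then n = 2 × (1.960 + 0.842)² × 4.57² / 2.72² = 2 × 7.849 × 20.885 / 7.398 = 44.3, so 45 per group. 45 / 0.90 = 50 per group, 100 in total. The evaluable numbers are thus 45 per group and 90 overall.

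**Exact result with no change in the others.** Let k of n participants rise by the same amount D and the rest change by zero. The mean is kD/n and the variance is D²k(n − k)/[n(n − 1)], so

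t = √[k(n − 1)/(n − k)].

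D cancels. Unequal positive rises give a smaller t: with S the sum and Q the sum of squares of the changes, t² = (n − 1)S²/(nQ − S²). This increases with S²/Q, which is at most k and equals k only when the rises are equal.

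| n | k | t | p |
|---|---|---|---|
| 50 | 1 | √(49/49) = 1.00 | 0.32 |
| 50 | 2 | √(98/48) = 1.43 | 0.16 |
| 50 | 3 | √(147/47) = 1.77 | 0.08 |
| 50 | 4 | √(196/46) = 2.06 | 0.044 |
| 100 | 3 | √(297/97) = 1.75 | 0.08 |
| 100 | 4 | √(396/96) = 2.03 | 0.045 |

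**Simulation with background variation.** Assumptions that are not in the article: ULN 40 U/L, median ALT 22 U/L, between-person log-SD 0.35, within-person log-SD 0.15 or 0.25, no true shift in the others, and k participants set to 3.5, 5 or 10 × ULN at week 8. There were 3,000 runs per setting. Entries are the percentage of runs with p < 0.05, as the range over these settings.

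| k | t-test, n = 45 | signed-rank, n = 45 | t-test, n = 90 | signed-rank, n = 90 |
|---|---|---|---|---|
| 0 | 5.2–5.8 | 5.3 | 4.9–5.4 | 4.9–5.2 |
| 1 | 0–0.8 | 4.0–5.2 | 0–2.5 | 4.7–5.3 |
| 2 | 0–3.4 | 5.6–7.0 | 0–6.3 | 5.2–5.6 |
| 3 | 0–16.0 | 8.4–9.5 | 0.1–18.3 | 6.6–7.6 |
| 5 | 84.5–100 | 18.2–19.5 | 70.4–100 | 10.7–12.8 |

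With one to three cases, the t-test is least likely to be significant when the rises are largest. With five cases it usually is significant, but the signed-rank test still is not. Section 2.8.1 chooses between the same two tests by normality. If that rule also governs 2.8.3, which the article does not say, large outliers would push the choice towards the signed-rank test.

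**What a count gives.** It shows every case. If 2% of participants truly exceed the limit, the chance of seeing at least one in 90 is 1 − 0.98⁹⁰ = 84%. With none in 90, the one-sided 95% upper bound is 1 − 0.05^(1/90) = 3.3%, and the upper end of the exact two-sided 95% interval is 1 − 0.025^(1/90) = 4.0%. By formula, assuming an equal split of 90 / 3 = 30, that upper end is 1 − 0.025^(1/30) = 11.6%.

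**The case against.** The strongest reply is that laboratory safety does not rest on the paired test alone. Section 2.8.3 puts adverse events first and adds the laboratory tests to them, and 2.9.1 makes any change that the investigator finds clinically significant a reportable event. A marked ALT rise fits that wording, and investigator observations could include laboratory results. This stands, and a reader who infers that a severe rise must go unreported goes further than the article allows. What remains is that the route has no fixed criterion and does not name laboratory tests, and that an enzyme rise without symptoms will not be self-reported.

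A second reply is that threshold counts and shift tables are often left to the full protocol or analysis plan, which is not shown. This also stands: their absence here does not show that the plan lacks them. The point concerns the test that the article does name.

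Third, the limits in 2.2.2 apply at screening. A reader might infer that a participant above them at week 8 breaches an on-treatment safety limit of the trial, but the article sets none. Nor does it say that a non-significant paired test will be read as evidence of safety.

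Finally, zero change in everyone else is an idealisation, and the ALT distributions are assumed. The simulation relaxes the first and gives ranges for the second. It also shows that the insensitivity is not absolute, since five cases usually make the t-test significant.

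**Conclusion.** The concern holds in a limited form. The one analysis that the article states for AST, ALT, BUN and creatinine is poorly suited to finding isolated severe rises. With one to three such participants the t-test is significant in about 0–18% of runs and the signed-rank test in about 4–9.5%, mostly no more often than the 5% expected by chance. The algebraic result for the t-test needs no distributional figures but assumes no change in the others; the percentages rest on the assumed ALT values above. The adverse-event route reduces the risk of missing a case but leaves it to judgment. This is a weak choice of method that is cheap to improve. It is not an error that invalidates the safety assessment, and the article does not support saying that laboratory safety is judged by the paired test alone.

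**What to change.** 1. In 2.8.3, add the number and percentage of participants whose week-8 AST or ALT exceeds 3 × ULN, or whose creatinine exceeds 2 × ULN, with exact 95% confidence intervals and a baseline-to-week-8 shift table. Use the 2.2.2 limits as descriptive reporting categories only. BUN has no limit in 2.2.2, so it would appear in the shift table only.
2. Present these by formula received. Both randomised groups contain all three formulas, so a comparison of ACCORD with DISCORD could not link a signal to a product.
3. Keep the paired pre–post change as a descriptive summary.
4. In 2.9.1, name laboratory results among the sources of adverse events. No numerical trigger is proposed; the investigator's judgment stays as written.
5. Reconcile Table 1, which marks the blood test at screening only, with 2.1.1 and 2.5.3, which place blood sampling at screening and week 8. Either analysis needs the week-8 sample. The written-consent row of the table as available here carries no mark at all, so a mark lost in reproduction is possible and should be checked first.

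The cost is one extra table from values that 2.5.3 already plans, and one added phrase in 2.9.1. Isolated abnormal values will become visible and need comment, and the intervals by formula will be wide.
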